### Randomization

Participants will be block randomized to study conditions, using a 1:1 allocation ratio, according to a random number list, computer-generated using specialist software by an independent trial administrator. Randomization will occur between the consent session and the first (baseline) home visit. After completing the consent session, the researcher will phone the trial administrator, who will consult the random number list to allocate the participant to a condition. A unique identification code denoting the participant and the participant’s general practice will be allocated by the trial administrator, to permit matching of data across time points.

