### Exploratory trial

#### Study design

An exploratory two-arm pilot RCT will be undertaken to evaluate the intervention. Participants will be randomized to receive either the habit-based booklet (intervention condition), or an existing UK National Health Service (NHS) fact sheet on physical activity and sedentary behaviour in older adulthood (control condition). Assessments will be made at baseline, and 8 and 12-weeks post-baseline (follow-up). Participants will be blinded to condition, but owing to staffing constraints, the researcher administering the intervention will be required to obtain outcome measures, so will be unblinded. Primary outcome measures will be recruitment and attrition rates, and secondary outcome measures will be changes in behaviour, habit, health and wellbeing. The study was registered on the International Standard RCT Number (ISRCTN) Register^a^ (ISRCTN47901994) in January 2014. The trial start date differs from that stated on the ISRCTN Register (April 2014) because of multiple unforeseen delays. The new planned start date is September 2014, and the trial is scheduled to end in February 2015. Recruitment had not begun at the time of submission of this manuscript.

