**Participant flow.**

Study information packs will be sent by post by the practice to a random sample of at most 300 eligible patients, with additional mail outs conducted if response rates among the first 300 are low (below 20%). The study pack will contain a study invitation letter, information sheet and business reply envelope. All documents within the pack will feature unique codes that identify the practice and recipient number, permitting calculation of response rates. Both the invitation letter and information sheet will list eligibility criteria for consideration for entry into the study. A tear-off sheet for return to the research team will be provided, so that interested patients can self-report their eligibility, contact details and consent to be contacted further by the research team.

Those who return the tear-off sheet will be phoned by a research team member, and asked to confirm their age and retirement status. Patients’ physical capability will be assessed by asking them to confirm that they could comfortably participate for at least 10 consecutive minutes in a set of physical daily activities, chosen to cover stretching, strengthening, balance and aerobic activities, each of which feature in the intervention booklet (for example, walking, housework). Patients will self-report their physical activity and sedentary behaviour over the telephone, using an adapted and validated short form of the International Physical Activity Questionnaire, which documents daily activity and sitting [51], and measures of time spent in specific sitting-based activities [52]. Patients confirmed as eligible will be invited to an appointment with a researcher at the general practice, at which they will provide written consent. Patients will be asked to bring their invitation letter to this session, to allow recording of per practice recruitment rates. A baseline measurement and treatment administration session will be arranged to take place a week later at the participant’s home. Recruitment to baseline is due to cease in December 2014, owing to time constraints.

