### Study procedure

After consenting at the general practice, participants will be fitted with a waterproof accelerometer (activPAL3; PAL Technologies, Glasgow, Scotland) to wear continuously (day and night) for one week. Our preliminary work indicated that participants wished to complete questionnaires in their own time, and so a questionnaire of self-report behaviour, health and wellbeing measures will also be given at this point, for completion over the following week. One week later (that is, baseline), the patient will be visited at home and the accelerometer and questionnaire collected, objective measures taken and the intervention or control treatment administered. Further home visits will be conducted at 7 and 11 weeks post-baseline to fit patients with an accelerometer and give a further questionnaire, and at 8 and 12 weeks post-baseline, to collect accelerometers and questionnaires and obtain follow-up objective measures. Participants will be contacted by phone at 4 weeks to arrange the 7-week home visit. Each subsequent visit will be arranged at the previous visit. If a participant is not home for a scheduled visit, the visit will be rearranged by phone where possible. Where participants are not contactable by phone, a maximum of two letters (at 4-day intervals) will be sent to invite them to arrange follow-up home visits. Those who do not respond to the second letter will be treated as having dropped out of the study. Participants will receive a £10 shopping voucher at the baseline, 8-week and 12-week home visits, in recognition of their help in facilitating intervention assessment. They will also receive a further £30 shopping voucher at 12-week follow-up, conditional on having attended all home visits and returned the accelerometer.

Intervention and control treatments will be delivered to each participant individually by postgraduate or postdoctoral psychology researchers trained in describing the intervention and carrying out all necessary study procedures. Participants will be given and talked through the main messages of the appropriate booklet, and will have the opportunity to ask questions if they do not understand any part of the booklet. Participants will be asked to contact the lead researcher if they lose their booklet, to request that another free copy be sent by post. The active treatment period is 8 weeks.

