#### Psychological measures

Habit strength for generic physical activity and sedentary behaviour and, in the intervention group only, each of the behaviours recommended in the tips will be assessed using a single automaticity item, adapted to each focal behaviour. This item (‘(Behaviour X) is something I do without thinking’) is derived from the automaticity subscale of the Self-Report Habit Index (SRHI) [64, 65]. A single item was chosen on the basis of data emerging from the preliminary field test that suggest that participants struggle to understand SRHI items, or show understandings that deviate from those intended by researchers. The chosen item has shown satisfactory content and predictive validity, and convergent validity with its parent index [64].

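### Allocation precedes the baseline home visit, so the unblinded researcher can take the baseline physical measures knowing the arm, and early losses are already randomised

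*Protocol article*

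**What the plan says.** The Randomization section fixes the timing: "Randomization will occur between the consent session and the first (baseline) home visit". It also gives the mechanism. Once the consent session is over, "the researcher will phone the trial administrator, who will consult the random number list to allocate the participant to a condition".

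The text after Figure 1 (Recruitment procedure: patients) sets the gap: "A baseline measurement and treatment administration session will be arranged to take place a week later". Study procedure describes the home visit: the accelerometer and questionnaire are collected, then "objective measures taken and the intervention or control treatment administered".

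Study design states who measures: "the researcher administering the intervention will be required to obtain outcome measures, so will be unblinded". The reason given is limited staffing. The same section says: "Participants will be blinded to condition".

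Two further statements bear on the order of events. At the consent session, "a questionnaire of self-report behaviour, health and wellbeing measures will also be given at this point". Psychological measures and Table 1 schedule habit items at baseline for, "in the intervention group only, each of the behaviours recommended in the tips".

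Nowhere does the article say that the allocation is withheld from the visiting researcher until the baseline measures are complete.

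**The concern.** Baseline values should be recorded before anyone who can influence them knows the arm. Here the order is consent, allocation, baseline physical measures, treatment. Limited staffing explains why follow-up is unblinded, because one person does both jobs and knows by then what was delivered. It does not explain an unblinded baseline: the same person could measure first and learn the allocation second.

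Two things are at stake. First, timed walk, grip, chair rises, tandem standing and blood pressure depend to some degree on how the examiner instructs, encourages or records, and the between-group analysis is a comparison of change from baseline. Second, a person who drops out after the allocation call and before the visit has been randomised but has neither treatment nor physical baseline. The trial's purpose is to settle procedures for a definitive RCT, so an avoidable weakness in the order of events is worth removing before recruitment starts.

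**Working it through.** The article gives no figure to reproduce: the sample size is pragmatic, and no alpha, SD or expected dropout is stated. The finding rests on the sequence; the arithmetic only illustrates scale.

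**Sequence**

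| Step | Event | Section |
|---|---|---|
| 1 | Consent at the practice; accelerometer fitted, questionnaire handed out | Study procedure |
| 2 | Researcher phones; administrator allocates | Randomization |
| 3 | Home visit a week after consent: accelerometer and questionnaire collected, physical measures taken | Study procedure |
| 4 | Same visit: booklet or fact sheet delivered | Study procedure |

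The treatment-giver is the assessor (Study design), and steps 3 and 4 share a visit. So the person measuring at step 3 is the one who must bring the right material for step 4.

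**Effect of a baseline error**

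Inputs from the article: 120 participants at 1:1, so 60 per arm; t tests on change over the first 8 weeks (Analysis of secondary outcomes). Assumptions: normal approximation, two-sided alpha 0.05, no true effect, equal SD at both times, baseline to follow-up correlation r of 0.5 to 0.8, differential error of size b (in SD units) at baseline, and none at follow-up.

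- Bias in the change contrast, in absolute size: b.
- SE = √(2(1 − r)) × √(2/60). At r = 0.5 this is 1 × 0.183 = 0.183; at r = 0.8 it is 0.632 × 0.183 = 0.115.
- Type I error = 1 − Φ(1.96 − b/SE) + Φ(−1.96 − b/SE).

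| b | r = 0.5 | r = 0.8 |
|---|---|---|
| 0.1 | 8.5% | 13.9% |
| 0.2 | 19.5% | 41.0% |

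For b = 0.1 and r = 0.5, b/SE = 0.548, giving 1 − Φ(1.412) + Φ(−2.508) = 0.079 + 0.006 = 0.085.

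Adjusting for baseline would shrink the bias to r × b (0.05 to 0.08 for b = 0.1) but would not remove it.

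**Losses before the visit**

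Assumed 2%, 5% and 10% of 120: 2.4, 6 and 12 people. The completer analysis needs valid data at all three time points, so it omits them. For the physical measures, the last- and baseline-observation-carried-forward analyses have no observed value to carry. All three planned analyses of these measures therefore leave out people who were randomised.

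**Habit items**

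The questionnaire is handed over at step 1, before an arm exists, whereas the tip-specific habit items are for one arm only. The article does not say at which step those items are asked.

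**The case against.** The strongest counter-argument is that the same unblinded role also measures at 8 and 12 weeks. If expectation shifts the measurement by f at follow-up and b at baseline, the bias in change is f − b. Equal shifts cancel, and blinding only the baseline would leave f in full. This is algebraically right, and it means that the table above isolates the baseline part only. But cancellation needs shifts of the same sign and size. That cannot be assumed when a researcher may expect no difference before treatment and an improvement after it. Unblinded follow-up is a separate limitation, disclosed with its reason; the change proposed here does not remove it.

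The scope is also limited, and this stands. The measures affected are secondary outcomes of an exploratory trial. Accelerometry and the self-completed questionnaire come from participants described as blinded, before the visit, and are less exposed. The planned power calculation for the definitive trial uses self-reported physical activity, not these tests.

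Several stronger readings are tempting but not supported:

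- *The arm is known a full week ahead, by the same person throughout.* The text fixes only a point between consent and the visit, so the interval is up to about a week. That the researcher hears the allocation on the call is implied, not stated. Study procedure mentions researchers in the plural, so the consent-taker need not be the visitor.
- *Early losses disappear into the attrition outcome.* Analysis of primary outcomes reports attendance at each home visit by group, with reasons for drop-out where available, so losses before treatment can be separated out.
- *The tip-specific habit items cannot be collected as scheduled.* They could be asked at the home visit, after allocation and before the booklet. The text is silent on this, not contradictory.

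Figure 1, the participant flow, is not available here and could not be checked.

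**Conclusion.** The concern holds as a point about sequence. The text places allocation before the baseline visit and makes the unblinded treatment-giver the assessor at that visit. Five examiner-dependent secondary measures can thus be taken with knowledge of arm for no operational need, and people lost in the interval are randomised without a physical baseline.

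The size of either effect is unknown. The 0.1 and 0.2 SD errors, the correlations and the 2% to 10% losses are all assumptions, and the documents do not show that any bias will occur. Nor do they show that the proposed order would lower total bias under every pattern of follow-up error; it removes the baseline component. The primary outcomes are affected only in that losses before treatment are counted after randomisation, by arm and visibly.

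**What to change.** Reword the Randomization and Study procedure sections so that the home visit runs in this order:

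1. Collect the accelerometer and questionnaire.
2. Record all the physical measures.
3. Phone the administrator for the allocation.
4. In the intervention arm, ask the tip-specific habit items.
5. Deliver the booklet or fact sheet.

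Losses between consent and baseline then become pre-randomisation losses. They should still be reported, as one overall figure, because they inform the feasibility of the definitive trial.

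State explicitly that the tip-specific habit items are asked at step 4, since the questionnaire given at consent precedes allocation. Asking them of controls as well would supply a comparator but would show controls the recommended activities. That is an optional trade-off against contamination, not a necessary part of the change.

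The costs are small. The administrator must be reachable during home visits, and the researcher must carry both sets of material. The identification code that the administrator also issues would be better kept at the consent stage, because the accelerometer units are programmed with participants' codes. Everything else is protocol wording, and recruitment had not begun when the article was submitted.

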### Study procedure

After consenting at the general practice, participants will be fitted with a waterproof accelerometer (activPAL3; PAL Technologies, Glasgow, Scotland) to wear continuously (day and night) for one week. Our preliminary work indicated that participants wished to complete questionnaires in their own time, and so a questionnaire of self-report behaviour, health and wellbeing measures will also be given at this point, for completion over the following week. One week later (that is, baseline), the patient will be visited at home and the accelerometer and questionnaire collected, objective measures taken and the intervention or control treatment administered. Further home visits will be conducted at 7 and 11 weeks post-baseline to fit patients with an accelerometer and give a further questionnaire, and at 8 and 12 weeks post-baseline, to collect accelerometers and questionnaires and obtain follow-up objective measures. Participants will be contacted by phone at 4 weeks to arrange the 7-week home visit. Each subsequent visit will be arranged at the previous visit. If a participant is not home for a scheduled visit, the visit will be rearranged by phone where possible. Where participants are not contactable by phone, a maximum of two letters (at 4-day intervals) will be sent to invite them to arrange follow-up home visits. Those who do not respond to the second letter will be treated as having dropped out of the study. Participants will receive a £10 shopping voucher at the baseline, 8-week and 12-week home visits, in recognition of their help in facilitating intervention assessment. They will also receive a further £30 shopping voucher at 12-week follow-up, conditional on having attended all home visits and returned the accelerometer.

Intervention and control treatments will be delivered to each participant individually by postgraduate or postdoctoral psychology researchers trained in describing the intervention and carrying out all necessary study procedures. Participants will be given and talked through the main messages of the appropriate booklet, and will have the opportunity to ask questions if they do not understand any part of the booklet. Participants will be asked to contact the lead researcher if they lose their booklet, to request that another free copy be sent by post. The active treatment period is 8 weeks.

### Intervention

For clarity, we report the content of our intervention with reference to the behaviour change technique (BCT) Taxonomy v1 [55]. The intervention booklet comprises text designed to promote motivation to form a habit, planning and self-monitoring to initiate and sustain change, and context-dependent repetition required for a habit to form [38]. The final intervention booklet will be made available on demand from the first author when the trial has ended.

Motivational text outlines the health detriments of prolonged sitting and the benefits of physical activity (BCT 5.1: ‘Information about health consequences’), and suggests reducing sedentary behaviour, either by directly substituting physical activity for existing sitting time (BCT 8.2: ‘Behaviour substitution’), or by promoting physical activity as a way of displacing sitting (BCT 4.1: ‘Instruction on how to perform behaviour’; BCT 13.2: ‘Framing/reframing’). The booklet explains that ‘physical activity’ refers not only to cardiovascular exercise, but also to stretching, balancing and muscle-strengthening exercises. It also describes and recommends the habit formation approach as a way of ingraining physical activity into daily routines, and provides guidance on how habits form (BCT 8.3: ‘Habit formation’).

Advice on forming habits is provided in the form of ten tips for physical activities that have the potential to displace sedentary behaviour and increase physical activity, and so improve health, wellbeing or functioning, and, if adopted and repeated consistently, lead to physical activity habit formation and disruption of sedentary behaviour habits (BCT 8.4: ‘Habit reversal’). The tips follow a template and feature catchy slogans to enhance memorability (for example, ‘take a stand’, ‘limber up’), brief descriptions of behaviour and the context in which it might best be done (BCT 1.4: ‘Action planning’), and, where appropriate, an explanation of how or why it will reduce sedentary behaviour or improve health or wellbeing. Additional ‘handy hints’ advise on how to move to higher-intensity variants of the recommended activity (BCT 8.7: ‘Graded tasks’), or ways to integrate the recommended activities into existing routines. Photos illustrate how to perform some tips (BCT 6.1: ‘Demonstration of behaviour’). The booklet is titled ‘On Your Feet to Earn Your Seat’, which reflects its recommendation that an empty seat be viewed as a cue to standing (BCT 7.1: ‘Prompts/cues’). Readers are encouraged to place the booklet on their favourite chair or on the kitchen table each evening to remind them to use it the following day.

Volitional support is provided in the form of a tick sheet with which participants can indicate whether they have achieved each of the tips at least once each day (BCT 2.3: ‘Self-monitoring of behaviour’; BCT 2.4: ‘Self-monitoring of outcomes of behaviour’), and advice on planning how to fit each recommendation into existing routines.

For those in the intervention group, the 4-week phone call to arrange the 7-week home visit will also provide an opportunity to discuss with a researcher any problems in adhering to the recommendations, or to obtain further motivational support (BCT 3.1: ‘Social support, unspecified’; BCT 3.2: ‘Social support, practical’).

### Control

Participants allocated to the control condition will receive an existing fact sheet outlining physical activity and sedentary behaviour recommendations for older adults [56]. This represents ‘usual care’ as a public health strategy for physical activity promotion among UK older adults. Since the intervention booklet details activities potentially beneficial to health in older adulthood, control participants will receive the intervention booklet on exiting the study.

### Measures

Table 1 outlines the study measurement schedule.

**Table 1 Tab1:** **Study measurement schedule: behavioural, health and wellbeing measures**

Measurement	Number of items	Objective measure or self-report	Construct measured	Measurement points		
				Baseline	8 weeks	12 weeks
***Behavioural***						
Accelerometry	-	Objective	Physical activity, sedentary behaviour	x	x	x
International Physical Activity Questionnaire (short form) [51]	7	Self-report	Physical activity, sedentary behaviour	x	x	x
Sedentary behaviour questionnaire [52]	7	Self-report	Sedentary behaviour	x	x	x
Tick sheet *(intervention group only)*	10	Self-report	Adherence to intervention	*Continuous use between baseline and 8 weeks*		
***Psychological***						
Item from Self-Report Habit Index and Self-Report Behavioural Automaticity Index [64, 65]	2	Self-report	Generic physical activity habit, Generic sedentary behaviour habit	x	x	x
Item from Self-Report Habit Index and Self-Report Behavioural Automaticity Index [64, 65] *(intervention group only)*	10	Self-report	Habit for behaviours recommended in intervention booklet	x	x	x
CONFbal [59]	10	Self-report	Confidence in balance	x	x	x
Short Falls Efficiency Scale, International [60]	7	Self-report	Fear of falling	x	x	x
***Health and wellbeing***						
Item from Fall Risk Assessment Tool [58]	1	Self-report	History of falls	x	x	x
Items from Center of Epidemiological Studies Depression Scale [61]	2	Self-report	Fatigue, exhaustion	x	x	x
Verbal descriptor pain item [62]	1	Self-report	Pain	x	x	x
Verbal descriptor stiffness item	1	Self-report	Stiffness	x	x	x
EQ5D [57]	6	Self-report	Quality of life	x	x	x
Timed walk	-	Objective	Walking speed	x	x	x
Grip	-	Objective	Grip strength	x	x	x
Chair rises	-	Objective	Leg strength	x	x	x
Tandem standing	-	Objective	Balance	x	x	x
Blood pressure	-	Objective	Blood pressure	x	x	x
